### Study outcome measures

The primary outcome in this project is the total emotional and behavioural problems score of the child according to the Child Behaviour Check List 1.5 - 5 (CBCL 1.5-5) at 18 months of age.

Secondary outcomes are the child's mental and psychomotor development at 18 months of age, the change in depressive and anxious symptoms in the mother, obstetric variables such as birth weight, gestational age and Apgar score, the socio-demographic and lifestyle factors, such as alcohol use, smoking and education, and cost-effectiveness of the therapy.

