### Sample size

Studies on the prevention of mental disorders tend to suffer from problems of insufficient statistical power [28]. In the current study we aim to get around this problem by using a continuous primary outcome measure and by including a high risk group (selective prevention).

We decided that effect sizes of 0.35 (midpoint of small - medium effect size) or over on the total problems scale of CBCL 1.5-5 are to be detected. With alpha 5% and power (1-beta) 80%, we have to include 260 participants in our analyses. To account for some drop out we aim at 300 women entering the trial. If 50% eventually meets all criteria and gives informed consent, 600 screen-positives must be identified. The 50% rate is based on studies with psychological interventions during pregnancy aimed at reducing the occurrence of postnatal depression [27]. Given the figures in the literature [11,29] we can expect around 10% screen-positives on either the anxiety or depression screener. With an estimated 50% comorbidity between anxiety and depression this means that approximately 15% will be eligible for the randomisation. Therefore, 4000 need to be screened. Assuming a response rate of 75% [30] this implies that 5333 must be offered screening. To be on the safe side, we aim at screening 6000 women. If necessary for the recruitment of 300 women, the total number of screens may be increased.

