### Assessments

Women will be asked to fill in questionnaires until their child is 1.5 years. This will be done at 8 occasions: the screener at baseline (T0), the additional baseline information (T1), and follow-up questionnaires at 24 and 36 weeks of gestation (T3 and T4), at 6 weeks postpartum (T5), 6 months postpartum (T6), 12 months postpartum (T7) and 18 months postpartum (T8).

At all time points, levels of anxiety and depression are monitored by the 6-item State Trait Anxiety Inventory (STAI) and the Edinburgh Postnatal Depression Scale (EPDS). As to be found in table 1, all other questionnaires can be filled in once or at several time points.

**Table 1 T1:** Assessments per measurement

	T0	T1	T2	T3	T4	T5	T6	T7
**Depression (EPDS)**	X	X	X	X	X	X	X	X

**Anxiety (STAI)**	X	X	X	X	X	X	X	X

**Personality NEO-FFI**		X		X		X		

**Life events before pregnancy (NLEQ)**		X						

**Life events during pregnancy**		X		X		X		

**Perceived social support (SSQ)**		X						

**Coping styles (UCL)**		X	X	X	X			

**Attitudes (DAS)**		X	X	X	X			

**Maternal attachment (ECR)**		X					X	

**Quality of life (EQ-5D)**		X	X	X	X	X	X	

**Sociodemographic & -economic factors**		X						

**Lifestyle**		X		X		X		

**Breastfeeding**						X		

**General health**		X						

**Health care consumption**		X			X	X	X	

**Previous pregnancies**		X						

**Suicidality (MINI)**		X						

**Clinical Diagnostic Interview (SCID-II)**		X						

**Child Behaviour (CBCL)**								X

**Child development (BSID-II)**								X

For anxiety, we use the Dutch version of the 6-item STAI. This self report questionnaire is as valid as the full 20-item version and has frequently been used to measure antenatal anxiety [29]. For the screening on depression we use the EPDS, which has 10 items [31]. This is the most frequently used self report depression screener in the postnatal period as well as during pregnancy and has been found particularly valid during pregnancy because this scale omits somatic symptoms [30].

The following information will be obtained from participants. The exact time of administration can be found in table 1.

• Life events before pregnancy will be assessed at baseline, using the Negative Life Events Questionnaire [NLEQ, [32]].

• Perceived social support will be measured according to the 9-item Social Support Questionnaire (SSQ)-short form [33].

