### CBT Intervention

The intervention consists of 10-14 individual sessions: 6-10 sessions during pregnancy and 4-8 sessions after delivery (once a week). The CBT will be conducted by registered psychologists, specialized in conducting CBT.

CBT posits that an individual's biased information processing leads to maladaptive feelings and behaviours which can culminate in psychological distress and eventually in psychiatric disorders. The main focus of the proposed intervention is targeted on identifying and changing dysfunctional cognitions and schemata (attitudes) specifically for pregnant depressed and anxious patients. In CBT, the Socratic dialog is used aiming to change these dysfunctional cognitions and attitudes permanently. CBT may therefore result in long term protection against psychosocial problems. It is therefore not surprising that cognitive therapy during the acute phase of depression also appears to be effective in reducing subsequent recurrence rates [25].

The first session will focus on the rationale CBT, i.e. the influence of (irrational or dysfunctional) cognitions and attitudes on feelings and behaviours. Additionally, goal setting will be initiated. These therapy goals will be unique for each patient. The subsequent sessions will be targeted at identifying and amending irrational cognitions and attitudes related to pregnancy, delivery, concerns about the (unborn) child and the future family situation. Each session will address specific pregnancy-related cognitions. Additionally, patients will be taught how dysfunctional cognitions and attitudes affect adversely feelings and behaviours.

These dysfunctional cognitions and attitudes will be challenged and replaced by functional cognitions and attitudes. After each session, patients will be given home work. For example, patients will be asked to register negative experiences, and accompanying cognitions, feelings and behaviours. Finally, in the last two to four sessions, the newly learned cognitions and attitudes will be consolidated.

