### Data analysis

If necessary, skewed continuous variables will be transformed to normality prior to the analyses. The primary outcome, i.e. the CBCL scores at month 18, will be compared between the treatment arms using the unpaired t-test. This test will also be used for detecting differences in the Bayley scores by month 18 and the obstetric variables measured at birth. The latter group of variables will be tested using the Chi2 test if categorical. Differences in attachment style at month 12 will be analyzed using analysis of covariance with the baseline variable as a covariate. Continuous outcomes that were measured more than twice (e.g. EPDS and STAI) will be analyzed as dependent variables using linear mixed models for fixed and random effects. These models are superior for the analysis of longitudinally correlated data and can optimally deal with missing values [53]. A mixed model ascribes a unique intercept and slope estimate to each individual, while making use of information across individuals for predicting these quantities. In these analyses, a treatment*time variable indicating the effect of the intervention will be included as an independent variable. If despite randomisation important baseline differences exist in prognostically important variables such as the extent of social support or history of life events, they will be adjusted for. Additional analyses will be conducted to demonstrate mediation of the effect of CBT on the child's outcomes by maternal symptom level, alcohol or nicotine consumption in pregnancy, medication use or neonatal outcomes.

The analyses will primarily be carried out according to the intention-to-treat (ITT) principle, i.e. the participants will be analyzed according to their randomized allocation, regardless of the actual CBT undergone, or time in study after baseline. Aside from the optimal validity of ITT analyses, they quantify the effects on the outcome measures that would be obtained in practice. The magnitude of the effect measured in an ITT analysis incorporates the effects caused by non-adherence to CBT, behavioural changes, et cetera. Secondary analyses will be of the 'per protocol' type meaning that they will be restricted to those women that had all of the CBT sessions.

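### Read as linear time, the treatment-by-time effect for EPDS and STAI dilutes a CBT benefit that appears early and is held, and all but misses one that fades

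*Protocol article*

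**What the plan says.** The Study outcome measures section lists "the change in depressive and anxious symptoms in the mother" among the secondary outcomes. The Data analysis section then states: "Continuous outcomes that were measured more than twice (e.g. EPDS and STAI) will be analyzed as dependent variables using linear mixed models". It characterises the method in these words: "A mixed model ascribes a unique intercept and slope estimate to each individual". It adds that "a treatment*time variable indicating the effect of the intervention will be included as an independent variable". It names no visit-specific or average contrast for these outcomes. It also does not say whether time is continuous or categorical, or whether a treatment main effect or the baseline score enters the model.

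Two other sections bear on the choice. Under Assessments, after the baseline measurements come "follow-up questionnaires at 24 and 36 weeks of gestation (T3 and T4), at 6 weeks postpartum (T5), 6 months postpartum (T6"), and then 12 and 18 months postpartum. Under CBT Intervention, the course is "6-10 sessions during pregnancy and 4-8 sessions after delivery (once a week"), and the therapy is described as "aiming to change these dysfunctional cognitions and attitudes permanently".

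**The concern.** One slope per woman, with one treatment-by-time variable as the effect, most naturally means that time enters linearly. The estimated quantity is then the rate at which the arms drift apart over about two years.

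The intervention does not predict that pattern. Weekly sessions in pregnancy and for a few weeks after birth should open a difference by late pregnancy or the early postpartum period. After that it should hold, as the therapy rationale hopes, or shrink. A slope describes neither course well, and three of the six follow-ups come at 6 months postpartum or later.

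At stake is the reported effect of CBT on maternal symptoms. This is a named secondary outcome, and the Background section calls symptom reduction valuable in its own right. A small or wrong-signed slope could be taken as no benefit in women who did improve while treated.

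**Working it through.** **The plan's own figure.** The only power statement concerns the primary outcome: "effect sizes of 0.35 (midpoint of small - medium effect size) or over on the total problems scale of CBCL 1.5-5", alpha 5%, power 80%, 260 analysed. It reproduces. The two-sided normal approximation gives 2 × (1.960 + 0.842)² / 0.35² = 128.1, so 129 per arm (258 in all). The t-test needs 130 per arm (260). No figure is given for the EPDS/STAI model, so the rest rests on assumptions.

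**Inputs.**
- From the protocol: the visit schedule, 1:1 allocation and 300 women entering (150 per arm).
- Assumed: baseline at 13 weeks and birth at 40 weeks of gestation, so visits at 0, 11, 23, 33, 53, 79 and 105 weeks; no missing data; intercept variance 0.5, slope variance 0.05 per year², residual variance 0.45; two-sided 5%.
- Assumed true differences, CBT minus usual care, in SD (negative is benefit):
  - Held: 0 at baseline, −0.4 at all six follow-ups.
  - Fading: 0, −0.25, −0.5, −0.5, −0.35, −0.2, −0.1.

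**Expected slope, baseline and treatment main effect in the model.** With a random intercept and slope and complete data, the expected coefficient is the least-squares slope Σ(t − t̄)d / Σ(t − t̄)². It depends only on the visit times and the profile, not on the variances. Here t̄ = 304/7 = 43.43 weeks and Σ(t − t̄)² = 8611.7.
- Held: Σtd = −121.6 and t̄Σd = 43.43 × (−2.4) = −104.23. The numerator is −17.37, the slope −0.00202 per week, about −0.105 SD per year.
- Fading: Σtd = −75.6 and t̄Σd = 43.43 × (−1.9) = −82.51. The numerator is +6.91, the slope +0.00080 per week, about +0.042 SD per year, which is the wrong sign.

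**Power.** The standard error is 0.051 per year. P(significant benefit) = Φ(−1.96 − z) and P(significant in the wrong direction) = Φ(z − 1.96).

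| Model | Held 0.4 SD | Fading 0.5 to 0.1 SD |
|---|---|---|
| Linear, with main effect | −0.105; benefit 55% | +0.042; benefit 0.3%, wrong direction 13% |
| Linear, no main effect (SE 0.048) | −0.150; benefit 88% | −0.013; benefit about 5% |
| Linear, follow-ups only, with main effect | exactly 0 | not needed here |
| Categorical, 36 weeks (SE 0.096) | −0.40; 98.6% | −0.50; 99.9% |
| Categorical, follow-up average (SE 0.069) | −0.40; above 99.9% | −0.317; 99.6% |

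The categorical rows constrain the arms to be equal at baseline.

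**Which visits drive the slope.** Shares of Σ(t − t̄)² are: 18 months 61.57²/8611.7 = 44%; baseline 43.43²/8611.7 = 22%; 12 months 15%; 24 weeks 12%; 6 months 9.57²/8611.7 = 1%.

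**Second set of assumptions.** This uses 130 per arm, baseline at 12 weeks, different variances and a 0.5 SD peak. Powers for benefit are with and then without a main effect.
- Build-up to 36 weeks, then flat: 80% and 99%.
- Fading to half by 18 months: 9% and 54%.
- Fading to zero by 18 months: 0% (38% wrong direction) and 2%.
- The categorical follow-up average has 94 to 100% power across the held and fading profiles.

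**The case against.** The strongest reply is that linear time is never stated. The intercept-and-slope sentence describes mixed models in general. Random slopes can sit beside categorical visit effects, and treatment by time is also ordinary shorthand for treatment-by-visit terms. A condensed article may leave the coding to a fuller analysis plan. This stands as a limit: if that plan makes visit categorical, the statistical problem disappears. It does not remove the point. The article itself names the variable that carries the effect, just after describing a slope per woman, and its natural reading is the unfavourable one.

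Several stronger readings are tempting and are not supported:
- **That an early benefit would generally be missed or reversed.** A held benefit is diluted, not lost, when baseline is in the model, and it is little harmed without a treatment main effect. With baseline modelled, reversal needs strong fading. For the 0.5 to 0.1 SD profile it also needs a main effect, which the text does not mention.
- **That the fading profile leaves 13% power.** That 13% is significance in the wrong direction; power for benefit is 0.3%.
- **That all the late visits dominate.** The 18-month visit does; the 6-month visit hardly counts.
- **That fading is what the trial expects.** The therapy rationale expects lasting change, and sessions may still be running at the 6-week postpartum visit. Fading is a risk to guard against, not a prediction of the document.
- **That the trial's main question is compromised.** The primary outcome is compared by t-test, and mediation through maternal symptom level is planned as a separate analysis.

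**Conclusion.** The concern holds as a badly fixed effect definition for a secondary outcome, conditional on time being linear. The direction of the problem follows from the visit times and the shape of the effect. The powers depend on the assumed variances, 150 women per arm and complete data, and would be lower with the 260 that the protocol expects to analyse.

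The size runs from moderate to severe. A held 0.4 SD benefit loses between about a tenth and nearly half of its power when baseline is modelled, and all of it when only follow-ups are. A benefit falling from 0.5 to 0.1 SD is practically invisible to any of the linear terms examined. How a reader of the results would interpret a null slope is a matter of judgement. The sample size of 260 analysed and 300 randomised is not in question.

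**What to change.** State in the Data analysis section that visit is a categorical factor with treatment-by-visit terms, and that the baseline score is a covariate or is constrained equal between arms. Define the treatment effect as the average difference over the post-baseline visits. Report visit-specific differences, for example in late pregnancy and at 18 months, each with a 95% CI. If a fuller analysis plan already does this, bring the intercept-and-slope wording into line with it.

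The change affects wording only and needs no extra data. It costs a few more parameters and some power if the effect truly grows linearly. Under the second set of assumptions, steady growth to 0.5 SD at 18 months is detected with 97% power by the slope (main effect in the model) against 89% by the follow-up average. That is a small price compared with the losses under the held and fading profiles.

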### Randomisation

Right after the SCID-II interview, women are randomised 1:1 to either CBT or CAU.

We will create randomisation lists, stratified for parity and socio-economic position, with randomly permuted blocks of random size.

Women randomized to the CAU arm will be informed about being at risk of depression or anxiety disorder by the researchers and will be advised to contact their GP. A close record will be kept of all care provided in the CAU arm.

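### The primary CBCL analysis is adjusted only if baseline differences look important, with no threshold, no closed covariate list and no stated status for the adjusted result

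*Protocol article*

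**What the plan says.** All places are in the protocol article, Methods/Design.

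- **Primary test (Data analysis).** "The primary outcome, i.e. the CBCL scores at month 18, will be compared between the treatment arms using the unpaired t-test". No covariates are named for it.
- **Conditional adjustment (Data analysis).** The trigger reads "If despite randomisation important baseline differences exist in prognostically important variables such as the extent of social support". The same sentence then gives a second example and the action to be taken: "or history of life events, they will be adjusted for". It comes after the mixed-model text but is not limited to it.
- **Allocation (Randomisation).** "Right after the SCID-II interview, women are randomised 1:1 to either CBT or CAU". The lists are stratified for parity and socio-economic position. Neither factor is carried into the primary test.
- **Sample size.** "With alpha 5% and power (1-beta) 80%, we have to include 260 participants in our analyses", for a standardised effect of 0.35, with 300 women to be entered.

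The article does fix a covariate in advance for another outcome: attachment style is analysed by analysis of covariance on its baseline value.

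**The concern.** Under randomisation a baseline difference between arms is a chance event. Its observed size is a poor reason to adjust; the strength of the variable's relation to the outcome is a good one, and that can be judged in advance. The protocol asks for both, since the variable must be prognostically important and must also differ between arms. The second condition makes the primary model depend on the sample drawn.

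Three things are left open: how large a difference counts, which variables are eligible, and which result is primary when the adjusted and unadjusted analyses disagree. Table 1 marks 17 instruments or domains at T1, so there is room for choice even within the prognostic ones.

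Two things are at stake. A faithful analyst loses the precision of planned adjustment whenever the arms happen to look balanced. A less disciplined analyst has more than one defensible primary result, and nothing in the text says which counts.

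**Working it through.** **1. The plan's own figure.** Inputs from Sample size: effect 0.35 with SD 1, alpha 5% (two-sided, because one-sided gives only 202), power 80%.

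n per arm = 2 × (1.960 + 0.842)² / 0.35² = 128.1, so 129 per arm and 258 in total. The t-based value is 129.1, so 130 per arm, which is the stated 260. Power at 130 per arm is Φ(0.35 × √65 − 1.96) = Φ(0.862) = 80.6%. The figure reproduces, and it rests on an unadjusted comparison.

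**2. How often the model would change.** The protocol gives neither a threshold nor a number of covariates, so these are assumptions. With 130 per arm, a standardised difference above 0.2 corresponds to z = 0.2 / √(2/130) = 1.61, which occurs by chance with probability 0.107 per independent covariate. The chance of at least one is 1 − 0.893^k. For a p < 0.05 trigger it is 1 − 0.95^k.

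| Trigger | 2 covariates | 6 covariates |
|---|---|---|
| p < 0.05 | about 10% | about 27% |
| difference > 0.2 | about 20% | about 50% |

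The undefined threshold and list therefore decide whether adjustment is a rarity or a coin toss.

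**3. Type I error, simulated with no treatment effect, 130 per arm.** Main scenario (assumed): 10 independent covariates, each correlated 0.15 with the outcome, trigger at a difference above 0.2. Range scenarios (assumed): 2 or 6 covariates, joint R² of 0.10 or 0.30.

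| How the model is chosen | Main scenario | Range scenarios |
|---|---|---|
| Fixed covariate set | about 5% | 4.8–5.2% |
| Trigger applied mechanically | about 4% | 3.6–4.7% |
| Better of unadjusted and imbalance-adjusted | about 6% | 5.2–5.6% |
| Single-covariate models also tried | about 8% | 7.4–10.6% |

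The last row's menus differ slightly. In the main scenario, single-covariate models are tried only for covariates differing by more than 0.1. In the range scenarios, every single-covariate model and the fully adjusted model are tried.

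The mechanical rule is conservative because it removes chance imbalance in just those trials where imbalance would otherwise have produced a false positive.

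**4. Power at 0.35.** In the main scenario the joint R² is 10 × 0.15² = 0.225, so the residual SD is √0.775 = 0.880. Power with a fixed set is approximately Φ(0.35/0.880 × √65 − 1.96) = Φ(1.245) = 89%. Chance imbalance in 10 covariates inflates the variance by about 1 + 10/258 = 1.04, which brings it to Φ(3.205/√1.04 − 1.96) = Φ(1.18) = 88%. Simulation also gives 88%. The unadjusted test, and the trigger applied mechanically, give about 80–82%.

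The gain depends on the assumed R². Before the small imbalance penalty, the same formula gives Φ(1.014) = 84% at R² = 0.10 and Φ(1.413) = 92% at R² = 0.30, against 80.6% unadjusted.

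**The case against.** The strongest reply has four parts.

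- **The trigger is not an outcome-driven choice.** It uses baseline variables, so looking at imbalance does not by itself show which model favours CBT on the CBCL. This stands. A reader might infer that the 5% level is necessarily exceeded; the document does not support that, and the mechanical rule is below 5%.
- **The 8% needs a menu the protocol never offers.** Nothing in the text provides for trying single-covariate models or selecting by result. This also stands, so that figure shows what loose wording would permit and does not describe the plan.
- **The t-test is stated without condition, and the adjusted analysis may only supplement it.** That reading is available, but so is the other, and the article does not choose between them.
- **Details belong in a SAP.** A threshold or list could be supplied there. But the article states a rule, and a SAP that merely added a threshold would keep observed imbalance as the trigger. The rule needs replacing.

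A reader might extend the same criticism to the sentence "If necessary, skewed continuous variables will be transformed to normality prior to the analyses". The document does not support that. It describes a distributional step taken before the arms are compared, its criterion is commonly left to the SAP, and a fixed skewness rule applied to pooled data without treatment arm held the error at 4.8–5.1% in simulation. Inflation would require choosing the scale by its p-value, which the text does not propose.

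**Conclusion.** The point holds for the adjustment rule alone. The main loss is efficiency: about 81% power against 88% at an effect size of 0.35, assuming 10 covariates each correlated 0.15 with the CBCL score. The gain from planned adjustment would be smaller with weaker covariates and larger with stronger ones. The secondary risk is discretion. Because threshold, list and status are open, choosing after results are seen could take the error to roughly 6%, or about 8% if single-covariate models were also tried. The covariate number, correlations and thresholds are all assumptions, since the document gives none. That the rule leaves the primary model undetermined does not depend on them.

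**What to change.** Replace the conditional sentence, for the primary outcome, with one pre-stated model: a linear model for the CBCL total problems score with treatment, the two stratification factors (parity and socio-economic position), and a short list of prognostic variables already collected at baseline, such as EPDS, STAI, social support and life events. Name the list before unblinding and use it whatever the observed balance. State that the treatment effect from this model is the primary result. Label any adjustment prompted by observed imbalance, and the unadjusted t-test if it is kept, as sensitivity analyses.

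The cost is wording in the protocol or SAP. No new data are needed, and 260 analysed and 300 entered can stand.

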Another indirect way in which depression might influence the offspring is when the antenatal depression remains after delivery and turns into a postnatal depression. In this way, mother-child attachment might be endangered, because the mother has a reduced ability to respond to the child. Children from depressed mothers have a higher risk on insecure attachment, which in turn is associated with cognitive, behavioural and emotional problems [1,18-20].

Finally, the association between antenatal depression and adverse outcomes in the offspring might be explained by genetic predisposition in both mother and child.

The effectiveness of psychological therapy in the treatment of both anxiety and depression has been shown in the past 50 years, especially for cognitive behavioural therapy (CBT) [21-25]. Although guidelines state that medication is an alternative effective treatment, the safety of antidepressants during pregnancy remains insecure [26].

Still, it is too early to implement CBT for depressed or anxious women to prevent psychosocial problems in the offspring. This is because in the development of such a preventive strategy, demonstration of the causality and size of the effect of the reduction of symptoms of depression and anxiety on child outcomes is a crucial step, a step that has not been taken to date. This knowledge gap will be filled by the results of the present experimental study.

Whatever the actual mechanisms involved are, there is presently convincing evidence that children whose mothers suffered from anxiety or depression during pregnancy constitute a high risk group for behavioural and emotional problems. On population level, substantial total mental health gains may be accomplished when depressed or anxious women are adequately treated during their pregnancy, even if the effect size of the treatment is relatively small.

We will perform a randomized controlled trial (RCT) in pregnant women with symptoms of depression or anxiety to study the effect of CBT as compared to care as usual (CAU) on the offspring's behavioural and emotional problems.

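### The mediation analyses aim to demonstrate a causal pathway that randomisation does not protect and that the article's own Background puts in doubt; they should be exploratory, adjusted and accompanied by a sensitivity analysis

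*Protocol article*

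**What the plan says.** All references are to the protocol article.

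- **Data analysis.** "Additional analyses will be conducted to demonstrate mediation of the effect of CBT" on the child's outcomes, with these mediators: "by maternal symptom level, alcohol or nicotine consumption in pregnancy, medication use or neonatal outcomes".
- **Background.** A crucial step not yet taken is "demonstration of the causality and size of the effect of the reduction of symptoms of depression and anxiety on child outcomes". The article says the present study will fill this gap.
- **Background, list of mechanisms.** One explanation offered is that "the association between antenatal depression and adverse outcomes in the offspring might be explained by genetic predisposition in both mother and child".
- **Randomisation.** "women are randomised 1:1 to either CBT or CAU". Nothing else is randomised.
- **Data analysis, covariates.** "If despite randomisation important baseline differences exist in prognostically important variables", such as social support or life events, they will be adjusted for. No other confounder adjustment is described. Attachment style is adjusted for its own baseline value, which is a separate matter.

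**The concern.** Randomisation protects two comparisons: CBT's effect on the mediator and CBT's total effect on the child. It does not protect the path from mediator to child. Every listed mediator arises after randomisation, and women with higher follow-up symptoms differ from those with lower ones in many ways besides the arm they were in. If something raises both the mother's symptoms and the child's problem score, the mediator-outcome coefficient is non-zero even when lowering symptoms does nothing for the child. Multiplied by a real CBT effect on symptoms, it gives a spurious indirect effect.

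The Background names such a common cause. The stated adjustment rule is aimed at a different problem: mediator-outcome confounding is present even when the arms are perfectly balanced. So an analysis meant to demonstrate mediation could attribute a CBT effect to symptom reduction when it came by another route. The Background itself expects other routes, including less smoking and drinking. The genetic remark concerns depression, but the lack of randomisation applies equally to the other listed mediators.

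**Working it through.** **1. The plan's own figure.** The Sample size section starts from "We decided that effect sizes of 0.35 (midpoint of small - medium effect size) or over", with alpha 5%, power 80% and 260 analysed. The two-sided normal approximation gives 129 per arm (258); the t-test gives 129.1, rounded up to 130 per arm (260). The figure reproduces, and 130 per arm is used below.

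**2. Inputs for mediation.** The article gives none, so these are assumptions:
- CBT lowers maternal symptoms M by a = 0.4 SD.
- A shared cause U gives a within-arm correlation r between M and the child score Y of 0.09, 0.16 or 0.25 (U loads 0.3, 0.4 or 0.5 on each).
- M has no effect on Y.
- Mediation is declared when the CBT-to-M path, and the M-to-Y path adjusted for arm, are both significant at two-sided 5%. The article does not specify this test.

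**3. CBT-to-M path.** Expected z = a × √(130/2) = 0.4 × 8.062 = 3.225. Power = Φ(3.225 − 1.96) = 0.897.

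**4. M-to-Y path, entirely spurious.** Expected z ≈ r√257 / √(1 − r²), where 257 is 260 less three fitted coefficients. The two tests are treated as independent. The spurious indirect effect is a × r.

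| r | expected z | P(M-to-Y significant) | × 0.897 | simulated (4000 runs) | spurious indirect effect |
|---|---|---|---|---|---|
| 0 | 0 | 0.050 | 4.5% | 4% | 0 |
| 0.09 | 1.449 | 0.305 | 27% | 27% | 0.4 × 0.09 = 0.036 SD |
| 0.16 | 2.598 | 0.738 | 66% | 65% | 0.4 × 0.16 = 0.064 SD |
| 0.25 | 4.139 | 0.985 | 88% | 89% | 0.4 × 0.25 = 0.100 SD |

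**5. Other assumed values.** A second simulation (2000 runs per setting) gave:
- a = 0.35 SD, r = 0.1, 0.2, 0.3: 29%, 72%, 81%.
- a = 0.5 SD, same r: 36%, 89%, 98%.
- a = 0: about 5% or less. The problem needs CBT to move the mediator.

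**6. Adjusting for a baseline symptom score.**
- If baseline and follow-up scores share only U, the partial correlation is (r − r²)/(1 − r²) = r/(1 + r), that is 0.083, 0.138 and 0.200. Simulated rates are 24%, 54% and 84%: little gain.
- If they correlate 0.5 (and each correlates r with Y), the M-to-Y coefficient falls to (r − 0.5r)/(1 − 0.25) = 0.67r. Simulated rates at r = 0.1, 0.2, 0.3 are 15%, 43%, 76% (a = 0.35) and 14%, 45%, 84% (a = 0.5): a larger gain in most settings.

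The benefit depends on the model, and neither version returns the rate to about 5%.

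**7. If a significant total effect on the child is also required.** At a = 0.4 and r = 0.09, 0.16, 0.25:
- CBT has no effect on the child: 1.3%, 3.3%, 4.6%.
- CBT has a true 0.35 SD effect, none of it through symptoms: 23%, 52%, 72%.

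**The case against.** **The main conclusion does not depend on mediation.** A reader might infer that the trial's causal claim stands or falls with this analysis. The article does not support that. The Objective is the effect of CBT against care as usual, tested by intention to treat with a t-test. Mediation takes one sentence among additional analyses and is not among the listed outcomes. This stands. What remains is that the Background words the gap to be filled as an effect of symptom reduction, which the randomised contrast alone does not isolate.

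**The method may be set out elsewhere.** An article may leave the mediation model, covariates and decision rule to the full protocol or analysis plan. That also stands, and their absence is not the point. The point is a stated aim and a stated causal conclusion that go beyond what is randomised.

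**The rates are built on assumptions.** Neither the CBT effect on symptoms nor the residual correlation is given, and the Background says only that genetics might explain the link. A reader might take its figure of up to 22% of variance in behavioural problems as proof that the assumed correlations are modest. It is not: it is a maximum for an association in observational work, not a measure of confounding, and this trial enrols only women above a symptom threshold, which would usually lower the correlation.

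**Mediation of an effect presupposes an effect.** If analysed only after a significant total effect, false mediation with no child benefit at all becomes rare (step 7). The article states no such condition. Even with it, a genuine CBT effect would often be credited to the wrong pathway.

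**Conclusion.** The point holds as a limit on what an additional analysis can show. The stated aim and the Background's causal wording exceed what the design identifies, because the mediators are not randomised, the article itself names a possible common cause, and the stated adjustment rule does not address it. The direction of the problem follows from the documents; its size does not. Under the step 2 assumptions, false mediation is declared in roughly 27% to 89% of trials against about 4% without a shared cause, with spurious indirect effects of about 0.04 to 0.10 SD. One baseline symptom score reduces this by a model-dependent amount and does not remove it. The consequence is misattribution of pathway. The primary result and the sample size are not in question.

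**What to change.** 1. In Data analysis, describe the mediation analyses as exploratory, and state that they assume no unmeasured confounding of mediator and outcome.
2. Adjust both the mediator and the outcome model for baseline common causes already collected, whatever the arm balance: EPDS and STAI, psychiatric history, personality, life events, social support and socio-economic position.
3. Report a sensitivity analysis over the residual mediator-outcome correlation, showing the value at which the indirect effect would reach zero. Step 6 shows why adjustment alone is not enough.
4. In the Background, limit the causal conclusion to the randomised CBT-versus-care-as-usual contrast.

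Cost: changes of wording and one extra analysis, with no new data and no change to the primary analysis or sample size. The drawback is a weaker mediation claim.
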